#### Patient data

Cluster-adjusted regression models will be used for all kinds of outcomes, with both dichotomous and ordinal variables. Cluster-adjusted analysis of variance and linear regression will be used for continuous and normally distributed variables. Mann-Whitney tests will be used for nonparametric variables. The cluster-adjusted chi^2^ test (and cluster-adjusted logistic regression) will be used to compare proportions. Where appropriate, comparisons of arithmetic or geometric means will be performed. A possible substantively important imbalance arising on baseline variables will be controlled at the analysis stage, as adjustment for imbalanced variables. We intend to adjust for multiple comparisons, table-wise, by applying False Discovery Rate, based on the obtained *P* values.

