#### Primary outcome measures for patients

A patient questionnaire (Additional file 2) consisting of three validated self-report instruments and study-specific questions will be used. The primary outcome measure will be the mean total score in *The Clinical COPD Questionnaire* (CCQ) which is a validated, self-administered questionnaire specifically developed to measure clinical control in patients with COPD [14]. It consists of 10 items, divided into three domains: symptoms, functional state, and mental state (scale per each item: 0 = best, 6 = worst). The higher the score, the greater the negative impact on quality of life and health status. The final measure is the mean value of the 10 questions; Minimal Clinically Important Difference = 0.44 of the final score (mean value) [28]. We will adjust for CCQ at baseline and the CCQs with the minimum of 6 of 10 items replied will be included in the analysis. The CCQ is constructed as an ordinal scale, and the statistics will be analysed accordingly. However, since the CCQ, as most symptom scales, is practically an interval scale, we will present the results using the mean instead of the median, to be able to compare our observations with those of earlier studies [29, 30].

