### Statistical methods

The cluster randomised design provides protection against contamination across trial groups when trial patients are managed within the same PHCC [38]. All analyses will be performed on the individual level adjusted for clustering. Socioeconomic and demographic factors will be taken into consideration, by adjusting for these factors in the models. We have chosen mixed models because this method allows missing data on one of the two measurements. Primary analyses will include intention-to-treat analysis and per-protocol analysis.

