#### Physician data

Analysis of the Physician Questionnaires will be performed using cluster-adjusted statistics. The emerging numeric data will be analysed using the cluster-adjusted chi^2^ test in order to compare proportions, and cluster-adjusted logistic regression for odds ratios [39]. Alternatively, if data is not normally distributed, nonparametric tests will be used.

*P* ≤ 0.05 will be considered statistically significant. For statistical analysis we will use software programmes STATA (StataCorp. 2015. Stata Statistical Software: Release 14; College Station, TX, USA: StataCorp LP.) and PSPP (IBM Corp. Released 2013. IBM SPSS Statistics for Windows, Version 22.0. Armonk, NY, USA: IBM Corp.).

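### The Mann-Whitney route for patient outcomes carries no cluster adjustment, contradicts the plan's own rule, and is not clearly closed off for a skewed CCQ

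*Protocol article*

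**What the plan says.** The protocol article sets its general rule under Statistical methods: "All analyses will be performed on the individual level adjusted for clustering". The same paragraph commits to a model class and gives the reason: "We have chosen mixed models because this method allows missing data on one of the two measurements".

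Under Patient data, methods are assigned by type of variable:

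- Dichotomous and ordinal outcomes: "Cluster-adjusted regression models will be used for all kinds of outcomes, with both dichotomous and ordinal variables".
- Continuous, normally distributed variables: analysis of variance and linear regression, both cluster-adjusted.
- Proportions: a chi-square test and logistic regression, both cluster-adjusted.
- A further group: "Mann-Whitney tests will be used for nonparametric variables". No cluster adjustment is mentioned, and the group is not defined.

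For physicians, the Physician data section first promises cluster-adjusted statistics and then adds: "Alternatively, if data is not normally distributed, nonparametric tests will be used".

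For the primary outcome, the section Primary outcome measures for patients says "The CCQ is constructed as an ordinal scale, and the statistics will be analysed accordingly". It then treats the score as in practice an interval scale and reports means. It also promises: "We will adjust for CCQ at baseline".

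**The concern.** Centres are randomised, not patients. A standard Mann-Whitney test compares the two arms as if every patient had been randomised separately. When outcomes within a centre are correlated, the variance is understated and P values are too small. The test also has no place for baseline CCQ or for the socioeconomic and demographic factors the plan promises to adjust for, and it cannot use a patient who has only one of the two measurements. The sentence therefore conflicts with several of the plan's own commitments at once.

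Two features widen the problem. First, it is tests that are parametric or nonparametric, not variables, so the wording does not say which outcomes take this route. It invites a choice made after the distribution has been seen. Second, the primary score is described both as ordinal and as practically interval, while linear regression is kept for normally distributed variables. If the CCQ turns out skewed, the text can be read as leading to ordinal regression, a linear mixed model or a rank test. Any P values that are too small would also enter the False Discovery Rate adjustment, which is based on the obtained P values.

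**Working it through.** **Inputs from the protocol article**

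- Threshold: P at or below "0.05 will be considered statistically significant" (Physician data). Sidedness is not stated; two-sided is assumed.
- 11 clusters per arm, 230 patients per arm, ICC 0.01 (Sample size). The 230 is taken as given; the point does not depend on how it was derived.
- Mean cluster size m = 230/11 = 20.9. Equal cluster sizes are assumed.

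**Formula.** If a test ignores clustering, its statistic has variance close to the design effect DE = 1 + (m − 1) × ICC instead of 1. The true two-sided error at a nominal 5% is then 2 × [1 − Φ(1.96/√DE)].

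**Reference case.** At ICC 0, DE = 1 and the formula returns the plan's nominal 5.0%.

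**At the plan's ICC of 0.01.** DE = 1 + 19.9 × 0.01 = 1.199; √DE = 1.095; 1.96/1.095 = 1.79; error = 7.35%.

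**Check by simulation.** The formula is an approximation for a rank test, so Mann-Whitney itself was simulated with no true effect: 11 clusters of 21 per arm, a CCQ-like score from 0 to 6 in steps of 0.1 (assumed mean 2 and SD 1.2 before truncation), 10,000 runs per ICC. A t-test on the cluster means was run on the same data.

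| ICC | DE | Formula | Mann-Whitney, simulated | Cluster-mean t-test, simulated |
|---|---|---|---|---|
| 0 | 1.000 | 5.0% | 5.5% | 5.3% |
| 0.01 (plan) | 1.199 | 7.4% | 6.8% | 4.9% |
| 0.02 (assumed) | 1.398 | 9.7% | 9.9% | 5.2% |
| 0.05 (assumed) | 1.995 | 16.5% | 15.8% | 4.7% |

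The Monte Carlo standard error is about √(0.05 × 0.95/10,000) = 0.2 percentage points at 5%, so the small departures from 5% at ICC 0 are noise. The excess at 0.01 and above is not.

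**Cluster size.** The expected baseline response gives 990 × 0.6/22 = 27 patients per centre. If all of these were analysed, the formula gives DE = 1.26 and an error of 8.1% at ICC 0.01.

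**Could the CCQ reach this route?** Read as ordinal, it goes to cluster-adjusted regression. Read as interval and normal, it goes to cluster-adjusted linear regression. Read as interval and skewed, the only entry under Patient data that names a test for it is Mann-Whitney. Only the general statements (adjust for clustering, use mixed models, adjust for baseline) argue against that reading.

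No figure is given for physicians, because the document states no ICC for their scores and does not name the test.

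**The case against.** The strongest reply is that the plan never sends the primary outcome to Mann-Whitney. A reader might infer that because the CCQ is called ordinal, a rank test is its stated route and the primary test is therefore inflated. The document does not support this: ordinal outcomes go to cluster-adjusted regression, and the promises of baseline adjustment, mixed models and clustering adjustment throughout all point to an adjusted model for the CCQ. Reporting means instead of medians is explained by comparability with earlier studies and does not show that the P value will come from a different analysis. This part of the reply stands.

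A missing label in a condensed article is also weak evidence. The sentence on comparing arithmetic or geometric means lacks the label too, and the general rule covers the whole section. That has some force, but regression, analysis of variance, chi-square and logistic regression are each labelled cluster-adjusted, and Mann-Whitney, the one remaining named test, is not. In its standard form it cannot meet the general rule. This is a contradiction in stated text, not a detail left to an analysis plan.

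For physicians, a reader might infer that the fallback tests ignore clustering. That cannot be known, because the tests are unspecified and the section opens by promising cluster-adjusted statistics. The fair complaint is that the fallback is loose.

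Finally, the inflation is modest at the only ICC the plan gives. This is correct. Higher values are assumptions, though the Discussion itself calls an assumed ICC a limitation and plans to compare it with the observed one. Small-sample corrections for the cluster-adjusted models are a separate matter: they concern a different test and add nothing to the Mann-Whitney figure.

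**Conclusion.** The point holds in a limited form. The Mann-Whitney sentence contradicts the rule that all analyses are adjusted for clustering, and the physician fallback sits loosely beside the promise that precedes it. The effect falls mainly on skewed secondary outcomes. For the CCQ the finding is an ambiguity, not a stated wrong test: the undefined class of variables, the normality condition on linear regression and the double description of the scale leave the route open for a skewed score.

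Followed as written for a patient outcome, a nominal 5% test has a true error of about 7% at ICC 0.01. If the true ICC were 0.02 or 0.05, the error would be about 10% or 16%. These figures assume two-sided testing, about 21 patients in each of 11 equal clusters per arm, and a standard Mann-Whitney test. The documents do not support saying that the planned primary test is inflated.

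**What to change.** 1. Under Patient data, delete the unadjusted Mann-Whitney route. For skewed or ordinal variables name a method that respects clustering: a cluster-adjusted rank test, mixed ordinal regression, a cluster bootstrap or a cluster-level permutation test. Name the outcomes it applies to.
2. Under Physician data, replace the unspecified nonparametric fallback in the same way.
3. For the primary outcome, state that the CCQ mean score is tested with the linear mixed model already chosen, with a random centre effect and baseline CCQ accounted for, whatever the observed distribution. The reported mean difference and its P value then come from one analysis. Specify the model so that patients with one of the two measurements stay in, for example with baseline and endline both as outcomes. A model for endline alone with baseline as a covariate would, without imputation, drop patients missing either measurement and lose the stated reason for choosing mixed models.

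The cost is a few sentences, slightly more analysis work and slightly larger P values. Recruitment and data collection do not change.

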#### Physician data

Analysis of the Physician Questionnaires will be performed using cluster-adjusted statistics. The emerging numeric data will be analysed using the cluster-adjusted chi^2^ test in order to compare proportions, and cluster-adjusted logistic regression for odds ratios [39]. Alternatively, if data is not normally distributed, nonparametric tests will be used.

*P* ≤ 0.05 will be considered statistically significant. For statistical analysis we will use software programmes STATA (StataCorp. 2015. Stata Statistical Software: Release 14; College Station, TX, USA: StataCorp LP.) and PSPP (IBM Corp. Released 2013. IBM SPSS Statistics for Windows, Version 22.0. Armonk, NY, USA: IBM Corp.).

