### Study design

This study involves a pragmatic and unblinded cluster randomised controlled trial (CRCT) with PHCCs as units of randomisation. In order to isolate the effect of CME, by Case Method, three groups (arms) will be established: one where CME by Case Method will be offered (arm 1, 11 PHCCs), one where traditional lectures (arm 2, 11 PHCCs) will be offered, and one where no CME will be offered at all (arm 3, 11 PHCCs). There will be a total of 33 PHCCs, or 33 clusters, from Stockholm County. From these, 180 PCPs (60 PCPs for each arm) and 460 patients (230 for arms 1 and 2, no patients for arm 3) will be asked to participate. Each PHCC will provide 25–30 patients, which will yield the minimum of 460 patients with COPD in GOLD stages 2 or 3 [2]. The outcome measures will be recorded at baseline and at follow-up which will be after 1 year for PCPs and 1.5 years for patients. The trial design is summarised in Fig. 1 and Fig. 2 as flow charts.

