### Outcome parameters and planned statistical methods

Outcomes are chosen for their ability to assess the effect of the interventions on both patient and PCP individually as well as on PHCCs as a whole (cluster). For data collection, validated questionnaires together with study-specific questions will be used. The baseline data collection will be completed prior the first CME session for the PCPs. Endline data for PCPs and patients will be collected 1 year and 1.5 years, respectively, after a completed CME.

The primary outcome of the study will be the effect of CME on patients’ disease-specific health status. Hence, the power calculations for the study have been performed on the basis of the primary outcome measure for patients rather than PCPs.

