#### Outcome measures for PCPs

The outcome measures for the PCPs pertain to individual participants. The Physician Questionnaire (Additional file 5) has been constructed by the researchers. The questionnaire is in fact an outright examination in line with the Constructive Alignment: the items cover the ILOs of S1–S3, leaving out the ILOs of S4–S5, as the latter ones will only be applicable for the intervention group, as shown in Table 1. The questionnaire is designed as an assessment test consisting of five short patient cases, with two to three questions per case (13 in total). The questions touch upon ‘knowledge/skills’ and ‘practical management’ yielding 0–2 points each, and appear as either:
*Multiple choice questions.* These questions mainly cover the areas of ‘knowledge/skills’, based on the ILOs concerning the current guidelines for COPD care. For instance, interpreting a spirometry result will be tested by a multiple choice question, implying one correct answer out of seven options. However, for questions such as on correct treatment of COPD exacerbation, several options can be ticked. A correct answer gives 2 points, partially correct 1 point, and all other replies result in 0 points

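### The physician examination yields graded scores, but the only named methods compare proportions; no score-level model or baseline term is given, and this does not match the mixed models announced for the trial

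*Protocol article*

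**What the plan says.** All references are to the Protocol article. Outcome measures for PCPs describes the questionnaire as an examination built on five short cases, "with two to three questions per case (13 in total"), the questions "yielding 0–2 points each". Study design sets two measurements: "The outcome measures will be recorded at baseline and at follow-up which will be after 1 year for PCPs". Outcome parameters and planned statistical methods adds: "The baseline data collection will be completed prior the first CME session for the PCPs".

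Physician data first states that the questionnaires will be analysed with cluster-adjusted statistics. It continues: "The emerging numeric data will be analysed using the cluster-adjusted" chi-square test, to compare proportions, and cluster-adjusted logistic regression for odds ratios. Then comes: "Alternatively, if data is not normally distributed, nonparametric tests will be used".

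Statistical methods, which stands above both the patient and the physician subsections, says that all analyses are adjusted for clustering and that "We have chosen mixed models because this method allows missing data on one of the two measurements". For the patient primary outcome, the article says "We will adjust for CCQ at baseline". Patient data lists linear regression and analysis of variance for continuous outcomes. Physician data has no counterpart to either statement.

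**The concern.** A chi-square test of proportions and a logistic regression are natural for yes/no outcomes. The examination gives three-level items, and a sum if they are added. To reach proportions, either the sum must be cut at a point that is not stated, or the questions must be tested singly. The first discards ordering. The second produces many tests, and the False Discovery Rate adjustment is described only under Patient data.

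The fallback adds to the doubt. Neither named method assumes a normally distributed outcome, so non-normality cannot be the condition for leaving them. The sentence makes sense only if a numeric-scale analysis is also intended, and none is named.

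This matters because Objective and hypothesis puts physician competence in the main aim and makes it the mechanism for patient benefit. The reference arm has no patients, so the questionnaire is also the trial's only outcome for comparing Case Method with no CME. The physician sample is small, and the Discussion says that there is no power calculation for it.

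**Working it through.** **1. Score range.** 13 questions × 2 points = 26, so a sum runs from 0 to 26. The article does not itself define a total score.

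**2. The plan's own physician number.** Recruitment of PHCCs gives five to ten eligible physicians per centre. Recruitment of PCPs gives 90% response and 20% dropout. At the midpoint, 33 × 7.5 × 0.90 × 0.80 = 178, against about 180 stated (60 per arm). The figure reproduces if 180 is read as the number after dropout. If it is the number before dropout, 60 × 0.80 = 48 per arm remain.

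**3. What the two sections imply.**

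| | Statistical methods (general) | Physician data |
|---|---|---|
| Model | mixed models | chi-square, logistic regression; nonparametric if not normal |
| Use of baseline | implied: two measurements, one may be missing | not mentioned |
| Clustering | all analyses adjusted | adjusted |
| Scale of outcome | not specific to physicians | proportions, odds ratios |

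The rows on model and baseline do not agree. The row on clustering does.

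**4. Information kept by a median split.** For a normal score this is 2/π = 0.637, so about 36% is lost. Against a baseline-adjusted score analysis, the fraction kept is (2/π)(1 − r²), where r is the baseline-to-endline correlation (not in the article):
- r = 0.3: 0.58, so 60 physicians work like about 35
- r = 0.5: 0.48, like about 29
- r = 0.7: 0.32, like about 19

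**5. Detectable difference at 80% power, two-sided 0.05.** Inputs from the article: 60 per arm and 11 centres per arm, so 60/11 = 5.45 physicians per centre. Assumed: ICC 0.05. The article's 0.01 was set in the patient calculation.
- Design effect: 1 + (5.45 − 1) × 0.05 = 1.22
- Multiplier with 20 degrees of freedom: 2.086 + 0.860 = 2.946
- Score, no baseline: 2.946 × √(2 × 1.22/60) = 0.59 SD
- Score with baseline: × √(1 − r²), giving 0.52 SD at r = 0.5 and 0.48 SD at r = 0.6
- Median split: effective n = 60/1.22 = 49 per arm. With the normal multiplier 1.960 + 0.842 = 2.80, solving p − 0.50 = 2.80 × √((0.25 + p(1 − p))/49) gives p ≈ 0.76, which is 0.71 SD on the underlying scale

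The split figure uses the normal multiplier and the others use t. With 2.946 throughout, the split gives p ≈ 0.77, or 0.75 SD, so the mix understates the gap.

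**6. Simulated check.** Rounded 0 to 26 scores, 11 against 11 centres, cluster-level t-tests, true difference 0.5 SD and r = 0.5 (both assumed), 60 per arm:

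| ICC | Median split | Score | Score with baseline |
|---|---|---|---|
| 0.01 | 54% | 73% | 83% |
| 0.10 | 47% | 60% | 67% |

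The ordering is the same at 48 per arm (ICC 0.01: 45%, 62%, 73%).

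**The case against.** Four points on the other side have force.

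First, a reader might infer that the physician analysis is planned without the baseline score. The article does not support that. Physician data is silent, and the general section implies that both measurements enter the model. Listing covariates for a secondary outcome is commonly left to a fuller document. What remains is that the two sections point to different analyses.

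Second, a reader might infer that the nonparametric fallback ignores clustering. It does not say so, and both the general section and the opening of Physician data require cluster adjustment. That reading should be dropped.

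Third, neither the total nor the median split is in the article. Comparing proportions of correct answers question by question is a legitimate use of the named methods, and its loss would not be the 36% above. A rank test on the score would keep about 3/π = 95% of the information under normality. The article therefore does not commit the trial to the loss calculated here.

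Fourth, the Discussion concedes that the questionnaire is not validated and that physician power was not calculated, and patient health status is the primary outcome. Making the unvalidated sum the main physician outcome is a choice with a cost.

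These points narrow the finding and make its size conditional. None supplies a coherent main analysis of the physician data.

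**Conclusion.** The point holds in a limited form. Physician data names only proportion-type methods for graded numeric data, qualifies them with a normality condition that does not apply to them, and does not agree with the mixed models announced above it. The main physician analysis is therefore not determined by the text.

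The size depends on how the wording is carried out. A median split would raise the detectable difference from 0.59 SD to about 0.71 SD, against 0.52 to 0.48 SD if the baseline score were also used. This is one scenario. It rests on a roughly normal sum score, an ICC of 0.05, r of 0.5 to 0.6 and 60 physicians per arm at endline. The direction was the same at every ICC (0.01 to 0.10) and r (0.3 to 0.7) tried. The loss under item-level testing was not calculated. The change is worth making, but the trial's primary patient outcome is unaffected.

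**What to change.** Reconcile Statistical methods with Physician data, and name one main physician analysis before endline data are analysed:
- **Outcome:** total score at one year.
- **Model:** linear mixed model with the baseline score as covariate and a random intercept for centre.
- **Main contrast:** Case Method against lectures, the randomised comparison. The reference arm was recruited separately and not randomised, so contrasts with it should be labelled as such.
- **Supporting results:** cluster-adjusted chi-square, logistic or ordinal models for single questions.
- **Fallback:** if a rank-based analysis is kept, tie it to the score model and state its cluster adjustment explicitly.

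The cost is wording only: the two planned measurements suffice, and no extra data are needed. The downside is reliance on the sum of a nonvalidated test, so the question-level results should be reported beside it.
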